[figure not shown]

**REVISION HISTORY**

| Revision # | Version Date | Summary of Changes                                                                                     |
|------------|--------------|--------------------------------------------------------------------------------------------------------|
| 1          | 10/22/2020   | CHOA/Grady Health System language added to consent                                                     |
| 2          | 06/24/2021   | Several questionnaires removed; pre-screening language added; screening questions added                |
| 3          | 10/22/2021   | Revision of EMA surveys                                                                                |
| 4          | 9/29/2022    | Added two additional data elements to chart review                                                     |
| 5          | 11/30/2022   | Added an over-the-phone/in-person semi-structured interview as a last point of contact to participants |

[figure not shown]

[figure not shown]

## 1. Study Summary

|                                                   |                                                                                                                                                                                                                                                                                                                                                                              |
|---------------------------------------------------|------------------------------------------------------------------------------------------------------------------------------------------------------------------------------------------------------------------------------------------------------------------------------------------------------------------------------------------------------------------------------|
| Study Title                                | Effects of social isolation on adolescent health during COVID-19                                                                                                                                                                                                                                                                                                             |
| Study Design                               | Prospective cohort                                                                                                                                                                                                                                                                                                                                                           |
| Primary Objective                          | To evaluate the feasibility of enrolling adolescents into a prospective cohort study that uses ecological momentary assessment and an activity tracker                                                                                                                                                                                                                       |
| Secondary Objective(s)                     | 

1. To quantify the effects of social isolation on adolescent mental and cardiovascular health metrics including physical activity, dietary quality, sleep, and heart rate variability

2. To identify factors that exacerbate or mitigate the effects of social isolation on adolescents during the COVID-19 pandemic

 |
| Research Intervention(s)/Interactions      | Study subjects will complete surveys using ecological momentary assessment and will wear an activity tracker which will measure physical activity, sleep, and heart rate variability                                                                                                                                                                                         |
| Study Population                           | Adolescents ages 13-18 years of age                                                                                                                                                                                                                                                                                                                                          |
| Sample Size                                | 20                                                                                                                                                                                                                                                                                                                                                                           |
| Study Duration for individual participants | 14 days, with option to continue to be contacted for up to 12 months                                                                                                                                                                                                                                                                                                         |
| Study Specific Abbreviations/ Definitions  | Coronary Heart Disease (CHD); Cardiovascular Disease (CVD); Clinical Research Coordinator (CRC); COVID-19 Experiences (COVEX); Electrocardiography (ECG); Ecological momentary assessment (EMA); General Anxiety Disorder-7 (GAD-7); Heart rate variability (HRV); Patient Health Questionnaire-9 (PHQ-9); Social Connectedness Scale (SCS);                                 |
| Funding Source (if any)                    | [name] Adolescent Medicine Research Fund (internal)                                                                                                                                                                                                                                                                                                                         |

## 2. Objectives

The purpose of this study is to evaluate the feasibility of enrolling adolescents into a prospective cohort study that uses ecological momentary assessment (EMA) and an activity tracker to quantify the effects of social isolation during the COVID-19 pandemic on mental and cardiovascular health. The objective is to collect pilot data on physical health metrics including physical activity, dietary patterns, sleep, and heart rate variability (HRV), along with measurements of social isolation, social connectedness, and

[figure not shown]

loneliness. These data will be used to apply for funding for a larger cohort study of the effects of social isolation on adolescent mental and cardiovascular health.

The specific aims are:

A1: Evaluate the feasibility of a prospective cohort study of social isolation in adolescence that utilizes ecological momentary assessment and activity tracking.

H1. A recruitment rate of 30% and a retention rate of 80% would indicate feasibility for a larger cohort study.

A2: To quantify the effects of social isolation on adolescent physical activity, dietary quality, sleep, and heart rate variability. Compared to adolescents who are less socially isolated, adolescents who are more socially isolated will have:

H2a: Lower physical activity as measured by an activity tracker

H2b: Less healthy diets as measured on by self-report

H2c: Later sleep onset and less consolidated sleep as measured by an activity tracker

H2d: Lower heart rate variability as measured by a heart rate monitor

A3: To identify factors that exacerbate or mitigate the effects of social isolation on adolescents. This exploratory aim will measure factors such as self-reported social connectedness, loneliness, social media use, adverse childhood experiences, peer victimization, discrimination, family cohesion, as well as sociodemographic factors including gender, race, family income, parental education, and neighborhood poverty level.

### **3. Background**

Social connection and support are associated with physical and mental health. The mechanisms by which social connection (defined as actual connections to others) and belonging (defined as perceived connections to others), and conversely social isolation (defined as lack of actual connections to others) and loneliness (defined as feelings of sadness due to perceived and actual connections to others), impact health are less well understood. Adolescence is a critical time in the life course for the establishment of mental health, cardiovascular health, and peer social relationships. A more comprehensive understanding of the mechanisms underlying the impact of social connectedness, belonging, social isolation, and loneliness on cardiovascular health during this unique developmental stage is needed. This gap in understanding has only increased in urgency with the COVID-19 pandemic.

Loneliness and social isolation are vitally important in early, middle, and late adolescence and in both girls and boys. Social support and meaningful daily interactions with others are inversely associated with loneliness, with especially strong correlation among young adults. Research indicates that children with persistently high loneliness have more depressive symptoms and lower self-perceived health. The

[figure not shown]

impact of the social isolation imposed by the COVID-19 pandemic on adolescents is therefore expected to be especially profound. Indeed, psychological distress increased from 3.7% in April 2018 to 24% in April 2020 among young adults ages 18-29 years, and 13.8% of adults reported always or often feeling lonely in April 2020.

In contrast to the data on mental health, the connection between social connection, social isolation, and loneliness and cardiovascular health across the life course is only beginning to be understood. In animal models, socially isolated animals develop more atherosclerosis than those housed in groups. In the few studies done with youth, children who were socially isolated from their peers had less optimal cardiovascular health metrics at 26 year of age and higher levels of inflammation as measured by c-reactive protein in midlife. In adults, social isolation and loneliness are associated with elevated c-reactive protein and later cardiovascular disease (CVD) death, as well as incident CVD events including a 29% increase in risk of incident coronary heart disease (CHD) and a 32% increase in risk of stroke, and future mortality in those with established CVD. Together, these studies establish a relationship between social connectedness, isolation, and loneliness and cardiovascular health while posing important unanswered questions about mechanisms, key developmental periods in the life course, and the impact of unique stressors such as the COVID-19 pandemic.

Potential mechanisms linking loneliness and social isolation with cardiovascular health include increased peripheral vascular resistance, increased inflammation and dysregulated HPA-axis activity. One established mechanism for assessing the impact of all of these systems on cardiovascular health is heart rate variability (HRV) as it reflects a complex interplay between the physiologic, cognitive, and emotional regulatory systems. In general, greater HRV is associated with greater capacity to respond to physical and emotional stress. HRV changes during adolescence, from the relatively higher HRV of childhood to the relatively lower HRV of adults.

HRV has been associated with both mental health and cardiovascular health outcomes. Baseline HRV is reduced in both adolescents and adults with depression and in adolescents with anxiety. Negative social interactions decrease HRV to a similar degree as the Trier Social Stress Task, and social isolation is associated with reduced HRV in adult women. Important developmental differences in HRV in response to stressors may occur. For example, animal models show a greater impact of social isolation on adolescent cardiovascular reactivity as compared to adult rats. In adults with depression, HRV is further blunted after stressful tasks but in adolescents with depression, HRV may actually increase after stressful tasks. Finally, HRV in adolescence is associated with other important lifestyle factors related to cardiovascular health including physical activity and sleep problems such as variable sleep duration and efficiency.

The figure below, from Holt-Lundstead and Smith, describes pathways linking social connection with cardiovascular health through mechanisms such as lifestyle factors, psychological factors, and biomarkers. In this proposal, we propose a feasibility study using ecological momentary assessment (EMA) and an activity tracker to understand the

[figure not shown]

effect of social isolation in real-time on adolescent behaviors/lifestyle, psychological functioning, and biomarkers relevant to cardiovascular health. This proposal is especially relevant now as adolescents are socially isolated to various degrees during the COVID-19 pandemic.

## Editorial

[figure not shown]

**Figure 1** Simplified model of possible direct and indirect pathways by which social connections influence disease morbidity and mortality.

Smaller studies have utilized both EMA and activity trackers and found both are feasible with adolescents, with 81% completing up to four surveys per day and 75% of adolescents wearing the activity tracker most days. A systematic review found wearable activity trackers are generally acceptable to adolescents in research studies, with wrist devices are more acceptable than hip and chest devices to teens. In addition to the physical health measures through the activity tracker, we will use EMA to capture adolescent perceptions of social connection, isolation, loneliness, and other emotional states in real-time. The most widely used measure of loneliness is the UCLA loneliness scale, which has been validated in adolescents ages 12-21. We will use this as well as the Social Connectedness Scale (SCS) and the PROMIS social isolation scale. Together along with self-reported social media use, peer victimization, and discrimination, the EMA and activity tracker will allow for a rich contextualization of the impact of degrees of social isolation due to the COVID-19 pandemic on adolescent mental and cardiovascular health.

## 4. Study Endpoints

The primary study endpoints are 1) feasibility (recruitment and retention rate) and 2) usability (% of days activity tracker is worn, % of EMA surveys completed, % of data that is interpretable). Secondary endpoints include objectively documented physical activity, sleep, self-reported diet, and heart rate variability.

[figure not shown]

## 5. Study Intervention/Investigational Agent

Participants will be fitted with an ActiGraph GT9X Link with accompanying Polar H7 Bluetooth Heart Rate Monitor. ActiGraph's activity and heart rate monitors are not subject to FDA regulation as they are not being used to diagnose or treat disease and are not introducing energy into the person's body. An accompanying manual will outline pertinent information regarding setup, initialization, data collection, and information for subjects. The manual has been uploaded with this submission in the "Other Documents" section (ActiGraph\_Link\_UserGuide.pdf).

Baseline surveys will collect data on validated scales of social connectedness, loneliness, social media use, adverse childhood experiences, peer victimization, discrimination, school climate, and family cohesion; physical and mental health including PHQ-9 and GAD-7; COVID-19 experiences; sociodemographic factors including gender, race, ethnicity, family income, and parental education; neighborhood poverty level and neighborhood-level movement/isolation via geocoding. EMA will use 4 surveys per day delivered via text to collect data on perceived social isolation, loneliness, and social media use. Survey responses will not be audio or video recorded for any participants.

## 6. Procedures Involved

### Study Schema

[figure not shown]

**Baseline Visit.** After providing informed consent, participants will complete the baseline study visit either in the CHOA Adolescent Research Room (in-person recruitment) or at home via Zoom (telehealth recruitment). The clinical research coordinator (CRC) will administer all baseline surveys via RedCAP either on a study iPad (in-person recruitment) or via a secure link sent to the participant's email. Participants will be taught how to apply the activity tracker and heart rate monitor. Height, weight, blood pressure, non-high density lipoprotein (non-HDL) cholesterol, and glycosylated hemoglobin (HbA1C) will be extracted from the medical record for baseline visits. For subjects approached about the study in person – regardless of if they complete their baseline visit at the clinic or at a later time via Zoom – their height, weight, blood pressure, non-high density lipoprotein (non-HDL) cholesterol, and glycosylated hemoglobin (HbA1C) measures will be extracted from their medical record using the clinical measures obtained during their intake exam on the day they were approached. For subjects

[figure not shown]

who enroll via telemedicine visits, their height, weight, blood pressure, non-high density lipoprotein (non-HDL) cholesterol, and glycosylated hemoglobin (HbA1C) measures will be extracted from their medical record using the clinical measures obtained during their intake exam on their most recent visit.

**During Study.** Participants will be monitored at home for daily social connectedness, isolation, loneliness, mood, activity, and autonomic function for 14 days, which is adequate to obtain stable estimates of heart rate and actigraphy indices of behavior based on prior studies. On day 14, subjects will remove the Actigraph and Bluetooth monitor and return them to us using a prepaid package or in-person during their end-of-study visit.

*Monitoring of Social Connectedness, Isolation, Loneliness, and Mood via EMA.* Following the approach of the MIDUS II National Study of Daily Experiences (NSDE), we will assess daily social connectedness, isolation, loneliness and negative/positive affect. Participants will randomly receive a text message four times per day for 14 days instructing them to complete the EMA surveys use an app called “RealLife Exp” which they will be instructed to download on their phone at the baseline visit. The RealLife Exp app is an iOS/Android app that will push notifications to participants’ mobile devices to alert them to complete daily surveys. Notifications will be pushed to the participants phone on a fixed schedule and participants will tap the notification allowing them to answer questions right away. The app will not collect any PHI and participants will be assigned a study ID which will help provide anonymity to participants when answering questions and allow the study team to link responses to other data collected on participants throughout the study. The study team will not be able to monitor any activity associated with participants’ mobile devices. The platform and data storage protocols for the app are HIPAA compliant. When subjects reach the end of the study duration, they will be instructed to remove the app from their phone. The research coordinator will walk participants through this process.

Participants will be sent a survey derived from the loneliness and distress questionnaire used by Yung et al, and containing questions surrounding overall connectedness. This survey will be sent to participants 4 times a day and will ask participants to rate these items based on their experiences over the past few hours. The survey will also contain questions surrounding passive and active social media use since social media has been associated with affect and social media use in youth and may or may not mitigate social isolation due to COVID-19.

*Activity Tracker.* Participants will record activity and sleep using actigraphy during the 14-day monitoring period. We will use the ActiGraph GT9X Link wristwatch-style actigraph containing a calibrated accelerometer that records movement activity in discrete epochs (30 s or 1 min) and detects physical activity as well as onset and offset of sleep. Sleep parameters are obtained using a scoring algorithm. Subjects will use the event marker on the ActiGraph to record any stressful events and will also keep a written log of these events, their intensity and triggers.

*HRV.* We will use the Polar H7 Bluetooth Heart Rate Monitor. Study staff will teach the participant how to apply the monitor during the baseline visit and instruct participants to wear

[figure not shown]

the monitor for up to 14 days, but for at least 24 hours. ECG data will be collected at 250 Hz sampling frequency and 10-bit resolution. We will not collect any PHI with the heart rate monitors. Instead, we will assign participants a study ID and use this for identification purposes. Raw ECG data will be sent to an Emory collaborating lab for analysis using custom-built validated software which will provide signal quality indices, abnormal rhythm detection, HRV indices and deceleration capacity.

The CRC will access the study logs via the activity tracker remote monitoring website daily and contact participants via text message if their device does not register data for 24 hours or no EMA assessments are completed for 24 hours.

**Study End.** Participants will be contacted by the CRC to document their consent to continue to be contacted for monthly surveys administered via use the “RealLife Exp” application. Participants who do not wish to continue will be instructed in how to remove the application from their phone. Participants who decide to be contacted for monthly surveys will continue to use the RealLife Exp app and receive notifications to complete EMA surveys once per month. After one year of follow-up for those consenting to the monthly EMA surveys, participants will be instructed in how to remove the application from their phone. No data will be collected after 1 year. Participants will be contacted via phone once more by the CRC for a semi-structured interview about their perspective on the study and its requirements. The CRC will also access their chart to view the date and time of their future appointments in the Adolescent Clinic at Children’s Healthcare of Atlanta at Hughes Spalding. Once participants come into the clinic for their appointment, the CRC will approach them to gauge their interest in the interview. If participants agree to participate in the interview, their answers will be collected as part of assessing the feasibility of the study.

All participants will be given a pre-addressed, stamped envelope in which to return the activity tracker and heart rate monitor after the 14-day study duration. No additional data will be collected from participants using these devices after the 14-day period.

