***Study Measures (see Appendix for details of specific measures)***

| Baseline                                     | During Study                                                           | Ongoing Monthly Surveys           |
|----------------------------------------------|------------------------------------------------------------------------|-----------------------------------|
| UCLA Loneliness Scale           | Yung’s Loneliness and Distress Scale 4x/day               | UCLA Loneliness Scale             |
| PROMIS Social Isolation Scale   | Alber’s Active and Passive Social Media Use Scale 4x/day  | PROMIS Social Isolation Scale     |
| General Social Media Use Scale  | Social Connectedness Questions 4x/day                                  | General Social Media Use Scale    |
| Georgia Student Health Survey 2.0            | Physical Activity via Actigraph continuously for 14 days               | Georgia Student Health Survey 2.0 |
| Everyday Discrimination Scale   | Sleep via Actigraph for 14 days                                        | Everyday Discrimination Scale     |

[figure not shown]

|                                                                                            |                                                                             |                                                                              |
|--------------------------------------------------------------------------------------------|-----------------------------------------------------------------------------|------------------------------------------------------------------------------|
| CYW Adverse Childhood Experiences Questionnaire for Adolescents: Self Report  | Heart rate variability continuously for at least 24 hours and up to 14 days | CYW Adverse Childhood Experiences Questionnaire for Adolescents: Self Report |
| McMaster Family Functioning Scale                                             |                                                                             | McMaster Family Functioning Scale                                            |
| COVID-19 Experiences (COVEX)                                                  |                                                                             | COVID-19 Experiences (COVEX)                                                 |

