### **17. Data Management and Confidentiality**

Given our proposed sample size of 20 participants, we have at least 80% power to detect a 0.53 standard deviation change from baseline to 3 months on a given outcome measure using a two-sided paired t-test with an  $\alpha = 0.05$ . We will report descriptive statistics for the EMA assessments. Paired t-tests (or if data are not normally distributed, the Wilcoxon signed-rank test) will be used to compare the baseline and monthly survey data for the continuous scales. Results will be presented as difference in means or medians with associated 95% confidence intervals. McNemar's test for correlated proportions will be used to compare binary outcomes including the baseline and monthly follow up survey data. Effect sizes will be calculated for all measures to further quantify the degree of efficacy. A recruitment rate of 30% and retention rate of 80% would indicate feasibility for a larger trial. Statistical analysis will be conducted using SAS v. 9.4 (Cary, NC) and significance will be assessed at the 0.05 level.

All questionnaire data will be collected using REDCap software. Data related to wearable devices will be collected using the manufacturer's software. To maintain participant confidentiality, all participants will be assigned a study identification number. The codes

[figure not shown]

that link the name of the participant and the study identification number will be kept confidential by the PI in a secured cabinet.

Upon data storage, all data will be de-identified. Only the authorized study team on this proposal will have access to the data. All study staff will complete biomedical or socio-behavioral training through the Collaborative IRB Training Initiative Program (CITI). We will store the data on the Emory server. The server is protected by the Emory network, and a secured log-in is required from all users. Data will be stored only until final analysis and publication of any manuscripts, after which the data files will be removed. No data will be released to other agencies.

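### The baseline questionnaires are repeated only in opt-in monthly surveys, so the planned changes from baseline describe those who opt in, while the power statement counts all 20 participants

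*Protocol*

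**What the plan says.** Section 1 sets participation at 14 days, with later contact optional for up to 12 months. In Section 6 (Study End) the coordinator contacts participants to document consent to monthly surveys. "Participants who decide to be contacted for monthly surveys will continue to use the RealLife Exp app"; those who decline are told how to remove it.

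The Study Measures table in Section 6 has three columns: Baseline, During Study and "Ongoing Monthly Surveys". UCLA Loneliness, PROMIS Social Isolation, COVEX, self-reported activity and self-reported diet stand in the first and third only. Section 8 places the PHQ-9 and GAD-7 within COVEX. The During Study column holds different instruments: EMA items on loneliness and distress, social media and connectedness four times a day, plus actigraphy and heart rate variability.

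In Section 17, paired t-tests or Wilcoxon signed-rank tests "will be used to compare the baseline and monthly survey data for the continuous scales", and McNemar's test does the same for binary outcomes. The power statement takes the full sample of 20 as its basis and says: "we have at least 80% power to detect a 0.53 standard deviation change from baseline to 3 months". The test it names is a paired t-test, two-sided.

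Other text points to a follow-up that the table does not contain. Section 6 lets devices be returned by prepaid package or "in-person during their end-of-study visit". Section 8 speaks of PHQ-9 and GAD-7 scores at a follow-up visit. Section 9 keeps participants who decline the monthly surveys enrolled for three months. Section 18 refers to safety monitoring at each follow-up visit.

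**The concern.** A change from baseline needs the same scale twice in the same person. On the schedule as written, the second measurement exists only for participants who agree, after the 14 monitored days, to go on. Willingness to continue may well be related to mood or loneliness, and these are the outcomes being measured. If so, the mean change among those who opt in differs from the mean change in the enrolled sample. A later analysis cannot recover scale scores that were never collected.

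Section 17 does not allow for this: it treats all 20 participants as supplying a baseline-to-3-month pair. Section 2 says the pilot data will support a funding application for a larger cohort, and Section 17 promises effect sizes for all measures. Effect sizes from those who opt in could be carried into that design as if they described clinic adolescents in general.

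**Working it through.** **1. Who supplies a pair**

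| Source of data | Who gives it | Change from baseline on the same scale? |
|---|---|---|
| Baseline questionnaires | all participants | first measurement only |
| EMA, 4 × 14 = 56 prompts | all participants | no; different items, no pre-monitoring value |
| Monthly surveys | those who opt in at Study End | yes |
| End-of-study or follow-up visit (Sections 6, 8, 18) | unclear | no scale scheduled in the table |

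So every pair entering the Section 17 comparisons comes from the third row.

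**2. The protocol's own power figure**

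Inputs from Section 17: n = 20 pairs, change 0.53 SD, two-sided paired t-test, α = 0.05. Power comes from the noncentral t distribution with n − 1 degrees of freedom and noncentrality d√n = 0.53 × √20 = 2.37. The result is 61.4%, not at least 80%. The normal approximation gives 65.9%, and one-sided versions give 73.9% (t) and 76.6% (normal). None reaches 80%. At 80% power, 20 pairs detect 0.66 SD; 0.53 SD needs 30 pairs. This error is separate and is present even if everyone opts in.

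**3. Precision lost through opting out**

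The opt-in rate is not stated, so the shares below are assumptions. The half-width of the 95% confidence interval for mean change, in SDs of the change, is t(0.975, n − 1)/√n.

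| Pairs (share of 20) | Half-width | Power for 0.53 SD | Change detectable at 80% power |
|---|---|---|---|
| 16 (80%) | 2.131/4 = 0.53 | 51.0% | 0.75 SD |
| 10 (50%) | 2.262/3.162 = 0.72 | 32.3% | 1.00 SD |
| 8 (40%) | 2.365/2.828 = 0.84 | 25.5% | 1.16 SD |

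**4. Possible selection bias**

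Assume that willingness to continue is normally distributed, that participants above a cut opt in, and that willingness has correlation r with the change score. The mean change among those who opt in is then shifted by r × φ(cut)/share, in SDs of the change. The ratio φ(cut)/share is 0.497 at 70% opt-in, 0.798 at 50% and 1.159 at 30%.

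| r (assumed) | 70% opt in | 50% opt in | 30% opt in |
|---|---|---|---|
| 0 | 0 | 0 | 0 |
| 0.1 | 0.05 | 0.08 | 0.12 |
| 0.3 | 0.15 | 0.24 | 0.35 |

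For scale, 0.24/0.53 = 0.45, so the middle value in the last row is a little under half of the change that Section 17 names. The documents give neither r nor its sign.

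**The case against.** A reader might infer that nothing is known about the enrolled sample after baseline and that those who opt out cannot be compared with those who continue. The protocol does not support that. Everyone is sent EMA items on loneliness, distress and connectedness for 14 days before the opt-in question. Early-to-late EMA change, and every baseline scale, can be compared by opt-in status. What stands is narrower: EMA gives no change from baseline on UCLA, PROMIS, PHQ-9, GAD-7, activity or diet.

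A reader might also conclude that no follow-up of everyone was ever intended. Sections 8, 9, 17 and 18 leave that open: a three-month assessment for all may have been planned and left out of the table. The contradiction is certain; which version is intended is not.

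Nor does the point reach the main aims. The primary endpoints in Section 4 are feasibility and usability. H2a to H2d in Section 2 compare more with less isolated adolescents, using baseline diet and 14-day device data. No numbered hypothesis concerns change from baseline.

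It is also fair to say that r = 0.3 has no source in the documents, that smaller n shows lost precision rather than bias, and that comparisons by opt-in status may be left to an analysis plan. Optional long follow-up is an open and reasonable choice in a 20-person pilot. Finally, a day-14 score measures a different interval from three months, and repeating the full battery would add burden in a study of feasibility. These objections limit the size of the point and shape the remedy. They do not supply the missing second measurement.

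**Conclusion.** The point holds in a limited form. On the schedule as written, the Section 17 changes from baseline apply to participants who opt in, and the power statement wrongly treats all 20 as contributing at 3 months.

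The structural gap is certain unless a follow-up for all was intended and omitted from the table. Bias is possible but not shown: zero if opting in is unrelated to change, and 0.15 to 0.35 SD at 70% to 30% opt-in under an assumed correlation of 0.3. The loss of precision is also conditional: with 10 to 16 pairs, power for 0.53 SD is 32% to 51%, against 61% with all 20.

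The stronger inference that the study's results as a whole are distorted is not supported, because the feasibility endpoints and H2a to H2d do not use the monthly surveys. The change is worth making but is not critical to the primary objective.

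**What to change.** 1. Reconcile Sections 1, 6, 8, 9, 17 and 18 on whether a follow-up visit or 3-month assessment exists for all participants. If it does, enter it in the Study Measures table with its scales.
2. If it does not, add a day-14 column to the table. At the Study End contact, before the opt-in question, give everyone only the scales that can change over two weeks: UCLA, PROMIS, the PHQ-9 and GAD-7 in COVEX, activity and diet. Leave out adverse childhood experiences, discrimination and family functioning. This would also supply the follow-up PHQ-9 and GAD-7 scores that Section 8 presupposes.
3. In Section 17, name baseline-to-day-14 change as the full-sample comparison. Label baseline-to-monthly change as applying to participants who opted in, and compare baseline, EMA and day-14 scores by opt-in status. Base the 3-month power statement on the pairs expected, with the assumed opt-in rate stated.

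Cost: one more short sitting of questionnaires already in use, at a contact already made. If paid at the monthly rate in Section 13, this is 20 × 5 = 100 dollars in total. The burden falls just after 56 EMA prompts, which is the reason for the short set. A day-14 score does not replace the 3-month comparison, which will still describe those who opt in.
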